**4. [Research method and period]**

① Research implementation period

From November 1, 2017 to March 31, 2021.

② Information on drugs used

Name: Tsumura Yokukansan (Product number: 054)

Route of administration, dosage and administration: Oral, 1 packet (2.5 g) at a time

Dosage form: Extract granules

③ Research subjects

Patients aged 20 to 60 years who undergo breast cancer surgery at Niigata University Medical and Dental Hospital or Niigata Prefectural Cancer Center Niigata Hospital and undergo total mastectomy and sentinel lymph node biopsy, or partial mastectomy and sentinel lymph node biopsy (Details will be described later).

④ Research method

Multicenter / Open Label / Superiority test by forced random sampling

[1] A pre-treatment questionnaire survey will be conducted on all subjects, and the age, BMI, surgical history, and general status (American Society of Anesthesiologists-Physical Status: ASA-PS, ECOG-PS) will be recorded in advance. Also, before taking the study drug, record the measurement of amylase in saliva, the Hospital anxiety and depression scale (HADS), and the State Trait Anxiety Inventory (STAI).

[2] Subjects are assigned to two groups, one with yokukansan (intervention) and the other without (control), according to the results of randomization. The intervention group should be given 1 packet (2.5 g) of TSUMURA Yokukansan before sleep on the day before surgery and 1 packet (2.5 g) 2 hours before entering the operating room on the day of surgery. For the purpose of maintaining the same quality between the two groups, a forced allocation algorithm is created, and if a bias is confirmed between the groups, forced allocation is performed based on age, surgical history, etc.

[3] Subjects in the intervention group take 1 packet of yokukansan orally 2 hours before entering the operating room on the day of surgery, and then all participants are measured salivary amylase in the operating room. Anesthetized by general anesthesia in the operating room and undergo total or partial mastectomy and sentinel lymph node biopsy

[4] Record salivary amylase measurements, HADS, STAI, visual analog scale of pain: VAS, QOR (Quality of recovery), and the presence or absence of analgesic use 24 hours after surgery.

| 24-hour before surgery | Salivary amylase  HADS STAI |
| --- | --- |
| Just before surgery | Salivary amylase |

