**5. [Policies for selecting research subjects]**

(1) Research subjects

① Patients aged 20 to 60 years who have been diagnosed with breast cancer and undergo total mastectomy and sentinel lymph node biopsy, or partial mastectomy and sentinel lymph node biopsy at Niigata University Medical and Dental Hospital or Niigata Prefectural Cancer Center Niigata Hospital

② Patients who received written and oral explanations regarding this study and showed their consent to participate in writing.

(2) Exclusion criteria

① Patients with preoperative condition classification (ASA-PS) 4 or higher by the American Society of Anesthesia

② Patients with BMI (Body Mass Index ≥ 30)

③ Patients who already have pain that requires oral painkillers somewhere in the body except for the primary disease

④ Those who are allergic to the drug used

⑤ Persons with hypokalemia

⑥ Patients taking anti-anxiety drugs and antipsychotic drugs

⑦ Patients who are already taking painkillers including opioids

⑧ Patients who have already taken some Chinese medicine

⑨ Patients who have difficulty communicating (dementia, mental retardation, mental illness, do not understand Japanese, etc.)

⑩ Other patients who are judged to be inappropriate by the principal investigator and the investigator

(3) Cancellation criteria

① When the research subject offers to decline participation in the research or withdraws consent

② When the entire research is canceled

③ When the result of intraoperative sentinel lymph node biopsy is positive and axillary lymph node dissection is performed

④ When the person in charge of research determines that it is appropriate to discontinue the research for other reasons.

(4) Voluntary research cooperation and freedom of withdrawal

Participation in the study is decided by the patient's free will, and it is possible to withdraw participation at any time. If the patient withdraws from the study before the start of oral administration, it will be excluded from this study. Patients who refuse to take the second dose after the first dose and withdraw from the study are also excluded from this study. Explain that withdrawal of research participation does not result in any disadvantage in subsequent treatment.

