**8. [Handling of personal information, etc.]**

All persons in charge of this study shall comply with the "Declaration of Helsinki (revised in October 2013)" and the Clinical Research Law. When publishing the results of the study, do not include information that can identify the subject. In addition, we will not use the materials of the subjects obtained in the research other than the purpose of the research.

**9. [Burden on research subjects and expected risks and benefits, comprehensive evaluation of these, and measures to minimize the burden and risks]**

Patients in the control group of this study do not take any medication and therefore do not suffer any benefit or disadvantage. On the other hand, patients in the intervention group have the disadvantages of having to take the drug even if it is difficult to take it, and the side effects of Chinese herbs may occur.

The side effects of yokukansan have been reported to be hypokalemia, gastrointestinal disorders (diarrhea and nausea), liver dysfunction, etc., but the frequency is stated to be less than 0.1-5% in the package insert. All of them are side effects of long-term continuous use (reported in 13 days at the earliest). Most of them occur in the elderly aged 65 and over. Since this time, the drug was taken only twice, it is highly unlikely that such side effects will occur. In the unlikely event that yokukansan causes health problems, the researcher will deal with it in good faith and provide appropriate medical care. The cost will be covered by the subject's insurance, and no special compensation will be provided by this study. The collection period for adverse events should be continuous from the acquisition of consent to the end of the study.

**10. [Procedures for collecting, recording, and reporting information on diseases, etc. (including identification of important diseases, etc. that the principal investigator should report to the principal investigator and abnormal values ​​of clinical tests, and requirements and deadlines for reporting) and outbreaks of diseases, etc. Observation period of subjects for later clinical studies]**

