**Procedures for handling missing, rejected and abnormal data**

If there is missing data on the primary endpoint, the patient's data will be excluded from the analysis. If it is found that missing data exists in the secondary evaluation item during data analysis, the item is treated as a deletion value and data analysis is performed.

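### Yokukansan patients who refuse the second dose and withdraw are excluded after randomisation, a rule that cannot apply to controls, and their data are discarded, so the randomised comparison cannot be recovered

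*Protocol*

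**What the plan says.** Section 4 describes the design as "Multicenter / Open Label / Superiority test by forced random sampling" and the allocation as follows: "Subjects are assigned to two groups, one with yokukansan (intervention) and the other without (control), according to the results of randomization". The intervention arm has two doses, one on the evening before surgery and "1 packet (2.5 g) 2 hours before entering the operating room on the day of surgery". Section 9 states: "Patients in the control group of this study do not take any medication". There is no placebo.

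Four provisions then remove patients or data after allocation:

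- Section 5(4), second dose: "Patients who refuse to take the second dose after the first dose and withdraw from the study are also excluded from this study".
- Section 5(4), before dosing: "If the patient withdraws from the study before the start of oral administration, it will be excluded from this study".
- Section 5(3), third cancellation criterion: "When the result of intraoperative sentinel lymph node biopsy is positive and axillary lymph node dissection is performed".
- Missing-data procedure at the end of section 12: "If there is missing data on the primary endpoint, the patient's data will be excluded from the analysis". The next sentence there treats a missing secondary item as missing for that item only.

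Section 12 also provides that, where participation is refused or discontinued after consent, the information collected so far is destroyed and collection stops. Nowhere does the protocol say that such patients stay in the analysis in their allocated group.

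**The concern.** Randomisation makes the two groups comparable when they are formed. A later exclusion keeps them comparable only if it works in the same way in both arms. The second-dose rule cannot do so, because a control has no dose to refuse.

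Section 9 itself recognises that intervention patients may find the drug hard to take and may have side effects. If those who leave for such reasons are also more anxious or more stressed, the yokukansan patients who remain look better than the group that was randomised, even if the drug does nothing. In a trial of about 40 per group, a handful of one-sided removals is enough to matter.

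A separate statistical analysis plan could normally settle the analysis set. Here the protocol fixes the exclusion and orders the data destroyed, so there would be nothing left to analyse.

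**Working it through.** **Which rule can reach which arm**

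| Rule | Yokukansan | Control | After allocation? |
|---|---|---|---|
| Refuses second dose and withdraws, 5(4) | yes | impossible | yes |
| Withdraws before oral administration starts, 5(4) | yes | can withdraw, but has no dosing event to mark the point | can be |
| Positive node with axillary dissection, 5(3) | yes | yes | yes |
| Missing primary value, section 12 | yes | yes | yes |

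Only the first rule is confined to one arm by construction.

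**The plan's own figure.** Section 4 gives power 80%, significance level 0.05, an intervention success rate of 75%, a difference of 0.3 and about 40 per group. Reading 0.3 as a difference in success rates (an assumption) puts the control rate at 45% and the pooled rate at 0.60. With a two-sided test:

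n = [1.960·√(2·0.60·0.40) + 0.842·√(0.75·0.25 + 0.45·0.55)]² / 0.3² = 40.7, or 41 per group.

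This reproduces the stated size. Power at 40 per group is 79.3%. Section 4 mentions no allowance for exclusions.

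**Bias on a continuous endpoint.** The documents give no refusal rate and no outcome for refusers, so the following are assumptions:

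- 40 per arm randomised, with no true effect;
- a fraction f removed from the yokukansan arm only;
- those removed have a mean D standard deviations worse than those retained.

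The full-arm mean is worse than the retained mean by f·D, so bias = f·D. With n₁ = 40(1 − f), SE = √(1/40 + 1/n₁) and z = f·D/SE, the type I error is Φ(−1.96 − z) + 1 − Φ(1.96 − z).

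| f | n₁ | SE | D | Bias (SD) | Type I error |
|---|---|---|---|---|---|
| 5% | 38 | 0.227 | 0.5 | 0.025 | 5.1% |
| 5% | 38 | 0.227 | 1.0 | 0.05 | 5.6% |
| 10% | 36 | 0.230 | 0.5 | 0.05 | 5.5% |
| 10% | 36 | 0.230 | 1.0 | 0.10 | 7.2% |
| 20% | 32 | 0.237 | 0.5 | 0.10 | 7.1% |
| 20% | 32 | 0.237 | 1.0 | 0.20 | 13.5% |

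**Success-rate scale, extreme case.** Both arms truly have 45% success and every removed patient is a failure. The observed yokukansan rate becomes 0.45/(1 − f), which is 47.4%, 50.0% or 56.2% for f = 5%, 10% or 20%. The type I error is about 5.5%, 7.2% or 15.6%.

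**Power.** At 75% against 45%, with loss in the yokukansan arm only, power falls from 79.3% to 78.2%, 77.0% or 74.1% (38, 36 or 32 left). If both arms lose equally, as the rules common to both arms would tend to produce, it falls to 74.9% at 36 per group and 69.6% at 32. Recruiting more, for example 40/0.9 = 44.4 or 45 per arm for a 10% loss, restores power but leaves the bias as it was.

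**The case against.** Several stronger readings are tempting, and the protocol does not support them.

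- **Refusing the second dose alone leads to exclusion.** The sentence requires refusal and withdrawal, and it stands in a paragraph on voluntary participation. A patient who refuses the packet but stays in the study is not addressed. Some of those removed may also have withdrawn consent to use of their data, which must be respected.
- **Withdrawal thins only the yokukansan arm.** Any patient may withdraw at any time, and in an open-label trial an untreated control may well do so. Only the second-dose clause is specific to one arm.
- **The axillary-dissection rule biases the comparison.** Nodal status is found during surgery and is very unlikely to be changed by two doses, so losses should be balanced in expectation. The criterion also fits the population defined in section 5(1). It does not itself order deletion; that follows only if cancellation counts as discontinuation under section 12.
- **A missing amylase value removes the patient from everything.** The contrast with the item-wise rule for secondary endpoints suggests this, but exclusion from the primary analysis alone is an equally possible reading.
- **The bias must favour yokukansan.** Calm patients may also decline a dose. Neither direction nor size can be read from the protocol, and with few refusals the effect would be small.

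It may also be said that the figure of about 40 could mean evaluable patients, and that the number is to be recalculated at the interim analysis. Both soften the concern about power. Neither touches the one-sided exclusion or the destruction of data, and that part of the concern stands.

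**Conclusion.** The protocol is wrong as written on a narrow but important point. It excludes a group of randomised patients that can exist only in the yokukansan arm, and it discards what was collected from them. Followed literally, it does not compare the groups as randomised, and no later analysis can repair this.

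With 5% to 20% removed and a deficit of 0.5 to 1.0 SD in those removed, the bias is 0.025 to 0.20 SD and the type I error about 5.1% to 13.5%. These figures rest on assumed refusal rates and an assumed direction; only the one-sidedness of the rule is certain from the text. The other exclusions are secondary: they cost numbers and precision, and the missing-data sentence is ambiguous about its reach.

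**What to change.** Amend section 5(4), the data-discard provision in section 12 and the missing-data procedure together, since changing one alone leaves the problem in place.

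1. Analyse all randomised patients in their allocated group.
2. State that a patient who does not complete the study doses stays in follow-up and in the analysis unless consent to data use is withdrawn.
3. Keep data collected before withdrawal or cancellation where consent permits. For axillary-dissection patients this includes the amylase value taken just before surgery.
4. Limit deletion for a missing value to the endpoint that is missing.
5. Report the number of exclusions and the reasons, by arm.
6. Keep the present exclusions as a per-protocol sensitivity analysis.

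These changes concern data retention and analysis only; they alter no dose or clinical procedure. The cost is a protocol amendment and a little more analysis. The estimated effect may be slightly diluted by patients who did not take both doses.

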**11. [Viewing original materials]**

At the conducting medical institution, the principal investigator ensures that all records, including source materials, can be viewed during monitoring, auditing and investigations by accredited clinical research review committees and regulators.

**12. [Method of storing and disposing of samples / information (including materials related to information used in research)]**

The information obtained from this study will be kept strictly until 10 years have passed after all research plans have been completed. Regarding the information obtained at all facilities, all or part of the information that can identify an individual is removed from the personal information and anonymized by numbering. The obtained patient information and questionnaire results will be stored in a locked drawer of the Niigata University Anesthesiology Laboratory in an anesthesiology state and will not be taken out. The correspondence table and patient information will be stored separately, and care will be taken to ensure that information is exchanged between hospitals appropriately. The person in charge of storage shall be [name], the person in charge of research. When discarding the obtained information, shredder the information left on the paper medium and erase the information left in the file format using data erasure software. The results of this research will be published by presenting them at academic meetings such as academic societies and academic journals, but in that case as well, consideration will be given to not being able to identify individuals, and the results of statistical analysis will be the main focus.

If the research is rejected or the research is discontinued after consenting to the research, all the information on the patients to be studied collected up to that point will be discarded and no further data will be collected.

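### Withdrawal linked to refusing the second dose removes randomised patients by a route open only to the intervention arm, and the protocol gives decliners no stated way to stay in the comparison

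*Protocol*

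**What the plan says.** Section 4 ④ describes the design as "Multicenter / Open Label / Superiority test by forced random sampling". Step [2] states: "Subjects are assigned to two groups, one with yokukansan (intervention) and the other without (control), according to the results of randomization". The intervention group takes one packet the night before surgery and one on the day of surgery. Section 9 says of the comparator: "Patients in the control group of this study do not take any medication". There is no placebo.

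Section 5 (4) gives two exclusion rules. The first is "If the patient withdraws from the study before the start of oral administration, it will be excluded from this study". The second is "Patients who refuse to take the second dose after the first dose and withdraw from the study are also excluded from this study".

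Three other rules bear on the point:
- Section 5 (3) ① cancels participation in either arm: "When the research subject offers to decline participation in the research or withdraws consent".
- Section 12 says that, if a patient who consented later rejects or discontinues participation, "all the information on the patients to be studied collected up to that point will be discarded and no further data will be collected".
- The paragraph on missing, rejected and abnormal data says: "If there is missing data on the primary endpoint, the patient's data will be excluded from the analysis".

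No section says what happens to a patient who declines a packet but is willing to be followed up.

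**The concern.** Randomisation makes the two groups comparable at the moment of assignment. A rule that later removes patients for a reason only one group can have may undo this. Here the second exclusion rule is tied to a packet that only the intervention group is offered.

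The protocol itself expects some reluctance: Section 9 counts having to take a drug that may be hard to take among the disadvantages for the intervention group. If those who refuse and leave are on average more anxious or distressed than those who stay, the remaining intervention patients would show lower amylase, HADS, STAI or pain scores even with an inactive drug. The t-test, the Mann-Whitney test and the Bayesian group difference in Section 4 ⑦ all take the remaining patients as given and cannot detect this.

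The loss is also permanent. If the data are discarded and collection stops, no analysis set defined later can bring these patients back.

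**Working it through.** **1. Who can be removed, and by which route**

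| Route | Intervention | Control |
|---|---|---|
| General withdrawal, Section 5 (3) ① | yes | yes |
| Leaves before dosing starts, Section 5 (4) | yes | only if read as a point in time |
| Refuses second dose and leaves, Section 5 (4) | yes | impossible, no dose exists |
| Data discarded on discontinuing, Section 12 | yes | yes |
| Missing primary endpoint | yes | yes |

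Only the third row is certainly confined to one arm.

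**2. The plan's own number**

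Section 4 ⑤ gives 75% success, 80% power, a significance level of 0.05 and about 40 per group. Reading the stated 0.3 as a difference in rates (an assumption, so 45% in controls) and the test as two-sided (also an assumption), with average rate 0.60:

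n = [1.960 × √(2 × 0.60 × 0.40) + 0.842 × √(0.75 × 0.25 + 0.45 × 0.55)]² / 0.3² = (1.358 + 0.555)² / 0.09 ≈ 40.7, so 41.

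This agrees with about 40, and 40 per arm is used below.

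**3. Size of the bias with an inactive drug**

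The refusal rate d and the correlation r between the tendency to refuse and a worse outcome are not in the documents. Both are assumed, as is no matching loss in controls. With a standard normal outcome, removing the top fraction d on the refusal tendency shifts the intervention mean favourably by

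bias = r × φ(z) / (1 − d), where z is the normal quantile at 1 − d and φ is the normal density.

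The standard error is √(1/40 + 1/n), with n = 40(1 − d) patients left. The false-benefit rate is 1 − Φ(1.96 − bias/SE).

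Worked case, d = 10% (4 of 40) and r = 0.5: φ(1.282) = 0.1755, so bias = 0.5 × 0.1755 / 0.9 = 0.098 SD. SE = √(1/40 + 1/36) = 0.230. The ratio is 0.424, and 1 − Φ(1.536) = 6.2%.

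| Refusal | r | Bias (SD) | False benefit |
|---|---|---|---|
| 5% | 0 | 0 | 2.5% |
| 5% | 0.3 | 0.03 | 3.5% |
| 5% | 0.5 | 0.05 | 4.3% |
| 10% | 0 | 0 | 2.5% |
| 10% | 0.3 | 0.06 | 4.4% |
| 10% | 0.5 | 0.10 | 6.2% |
| 10% | 1.0 | 0.20 | 13.3% |

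Simulated trials with a pooled t-test agree: at 10% refusal, the false-benefit rate was about 4.5% (r = 0.3), 6% (r = 0.5) and 14% (r = 1.0). The last is slightly above the formula because removing the extremes also shrinks the variance. The row r = 1.0 means that the refusers are exactly the worst patients, so it is an upper bound.

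**4. Direction**

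If the least anxious patients are the ones who see no need for the drug and leave, r is negative and the bias works against yokukansan.

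**The case against.** Several points on the other side stand.

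- Both sentences in Section 5 (4) require leaving the study. A reader might infer that patients are excluded merely for not taking yokukansan; the text does not say so. It is silent on the patient who declines a packet and stays.
- A reader might infer that the control group remains unselected. It does not: controls can withdraw at any time under Section 5 (3) ①, with the same data loss under Section 12. Equal selective loss in both arms would cause no bias.
- The first sentence can be read as a point in time, the evening before surgery, which a control patient can also precede. Only the second-dose sentence is securely arm-specific.
- No document links refusal to outcome. Difficulty with taking the drug may mean only that granules are unpleasant to swallow, and Section 9 regards side effects from two doses as highly unlikely. With no correlation there is no bias.
- Analysis sets are commonly left to the statistical analysis plan, which is not shown.

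The last point does not dispose of the matter. The complaint is not that an analysis set is undefined. The protocol states an exclusion after randomisation and, in Section 12, orders the data to be discarded. An analysis plan can choose among the data that exist but cannot restore data that were destroyed or never collected.

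**Conclusion.** The point holds as a structural defect of limited and unknown size. Section 5 (4) adds to ordinary withdrawal one route of exclusion that only intervention patients can take and that may be related to outcome. Section 12 makes the loss irreversible, and nothing in the protocol keeps a patient who declines a packet in the assigned group.

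Under the assumptions in the working (5–10% refusal, correlation 0 to 0.5), the bias runs from 0 to about 0.10 SD and the one-sided false-benefit rate from 2.5% to about 6%, against 2.5% nominal. The upper bound at 10% refusal is about 0.20 SD and 14%. The sign could be the opposite, and with one or two refusals the effect would be small unless those patients were extreme. It would be too strong to say that the trial is biased in favour of yokukansan: the documents give neither a refusal rate nor a link to outcome. They do set up a rule under which such a bias can arise and cannot later be checked.

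**What to change.** Change two places together.

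1. **Section 5 (4).** Replace the two exclusion sentences with wording such as: declining a dose is not in itself withdrawal from the study; every randomised patient who has not withdrawn consent to the use of data is assessed on schedule and analysed in the assigned group, whatever doses were taken; an analysis restricted to intervention patients who took both packets is supportive only.
2. **Section 12.** Limit the discarding of data to patients who withdraw consent to data use, and report the number and timing of such withdrawals by arm.

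Changing Section 5 (4) alone would leave the data loss in place. The rule on a missing primary endpoint need not change for this point, since a decliner who is assessed on schedule has the endpoint.

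The cost is a few sentences in two sections, with no added patients or visits. The downside is a slight dilution of the effect by intervention patients who did not take the drug. The change does not affect the dose, its timing or a patient's freedom to refuse or leave.
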